A blinded, the trained rater will assess mood each week, from baseline to 2 weeks after treatment, using the Montgomery-Asberg Depression Rating Scale (MADRS) scale. MADRS scale is more sensitive to change in patients’ mental condition than Hamilton depression rating scale [44]. The primary outcome is response rate, which are assessed at end of week 4 and week 6. Secondary outcomes include remission rate, Clinician Global Impression –Improvement Scale (CGI-I) and the self-rated Quick Inventory of Depression (QIDS-16). Patient’s cognition will be monitored using the Montreal Cognitive Assessment Scale (MoCA) before and after the 1-week active treatment period and quality of life (QoL) measured by the Quality of Life Enjoyment and Satisfaction Questionnaire – Short Form (*Q*-*LES*-*Q*-SF), assessed at baseline and end of week 2. MoCA is a brief cognitive instrument recommended for screening for cognitive impairment (CI) in patients. Several studies have compared the discriminant abilities of the MoCA and the Mini-Mental State Examination (MMSE) for screening post-stroke CI, and most studies have demonstrated that the MoCA is superior or equivalent to the MMSE for the detection of CI after stroke. Furthermore, the MoCA has been reported to be sensitive to changes in acute temporary CI after mild stroke/TIA, whereas the MMSE is reportedly not [45]. Therefore, in the current study, we use MoCA to assess acute changes in cognitive abilities.

After aTMS treatment, all subjects will then be followed up once a week for 2 weeks and subjects who achieve remission will exit the study.

#### Randomization at phase 2

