### Statistical analysis

Clinical, demographic characteristics and mood, cognitive, and QoL scores will be tested for any differences at baseline between the two randomized groups using *t test* or *chi-square* test wherever appropriate. The effect size of aTMS will be assessed by the proportion of response rate, which was defined as “Response: ≥50% MADRS score decrease from baseline” and “Non-response: <50% MADRS score decrease from baseline”. “Remission” is defined by score of 10 or less on MADRS score. Changes in mood and other ratings from baseline to each follow-up time point will be assessed with paired *t* test followed by repeated-measures analysis of variance (*ANOVA*)*.* Statistical tests will be two-tailed.

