
### Sample size calculation

Based on our center’s TMS results to date, patients start TMS treatment with an average MADRS score of 25.4 (SD 7.3), which decreases significantly to 18.4 (SD 9.9) after 2 weeks of treatment with standard rTMS and to 14.1 (SD 10.7) after 4 weeks of treatment. Participants enrolled in the study would be expected to have similar improvements in MADRS with aTMS treatment.

This study is powered to test the primary aim, i.e., a significant reduction in MADRS scores from baseline to end week 3, in the overall study sample. Based on the MADRS scores cited above for baseline (25.4 ± 7.3) and end week 4 (14.1 ± 10.7) time points, detecting a similar significant change after a course of aTMS would require a sample of 12 participants (alpha 0.5, 95% power). However, given the lack of data on the efficacy of aTMS in an Asian population, and to give a better estimate of response and remission rates, we anticipated that 60% of those recruited will drop out before the end of the trial with an unequal allocation ratio of 2:1, we thus aim to recruit 40 subjects in the delayed start arm and 20 subjects in the immediate start arm for a total of 60 subjects.

No prior data exist on the comparative effects of delayed response with immediate treatment of aTMS (or TMS), we will also explore the aim that non-responders to a 1-week course of aTMS will have a higher chance of response to a change in aTMS from L 5 Hz DLPFC TMS to R 1 Hz DLPFC for depression. This study will produce pilot data for 2nd and exploratory aim, informing the power analysis for a future clinical trial if results reject a null hypothesis.

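### Change from baseline is tested by a separate paired t test at every follow-up on every rating, and the confirmatory claim is not tied to any one of these tests

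*Protocol article*

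**What the plan says.** Statistical analysis: "Changes in mood and other ratings from baseline to each follow-up time point will be assessed with paired" t tests, followed by a repeated-measures ANOVA. The section adds that "Statistical tests will be two-tailed". It gives no test level and does not single out a rating or a visit.

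Sample size calculation: "This study is powered to test the primary aim, i.e., a significant reduction in MADRS scores from baseline to end week 3", in the overall sample. The Hypothesis section names the same contrast.

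Evaluation of clinical response at phase 1: a blinded "rater will assess mood each week, from baseline to 2 weeks after treatment, using the Montgomery-Asberg Depression Rating Scale (MADRS) scale". MoCA is taken before and after the treatment week, and Q-LES-Q-SF at baseline and end of week 2. On ranking, "Secondary outcomes include remission rate, Clinician Global Impression –Improvement Scale (CGI-I) and the self-rated Quick Inventory of Depression (QIDS-16").

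The primary is described differently from place to place:

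- Abstract: MADRS improvement at the end of the active treatment phase.
- Hypothesis and Sample size calculation: MADRS change to end of week 3.
- Evaluation at phase 1: response rate at weeks 4 and 6.
- Evaluation at phase 2: mean MADRS change to 4 weeks after treatment start and, as primary endpoint, a MADRS below 11 at any follow-up.

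**The concern.** The analysis paragraph fixes a method that yields one p-value per rating per visit and treats them all alike. If the rest of the article pointed to one primary contrast, a reader could pick out the test that matters. It does not: the candidate primaries fall at different weeks and use different summaries of the same scale. With a test at every week and several weeks that could be called primary, a favourable week could be presented as the main result.

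The ratings outside the powered contrast are exposed too. An isolated nominal result on QIDS or quality of life could be reported as an effect of accelerated TMS when it is chance. The Discussion and Conclusions intend the results to inform practice and treatment guidelines, so it matters which result is confirmatory.

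The rule also does not fit one listed secondary outcome. CGI-I rates improvement, so it has no baseline value with which to form a pair.

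**Working it through.** **The plan's own figure.** Inputs, from Sample size calculation: "Based on the MADRS scores cited above for baseline (25.4 ± 7.3) and end week 4 (14.1 ± 10.7) time points", so the expected change is 25.4 − 14.1 = 11.3. The within-patient correlation r is not given; 0.5 is assumed, with a range of 0 to 0.8.

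- SD of change = √(7.3² + 10.7² − 2r × 7.3 × 10.7). At r = 0.5 this is √(53.29 + 114.49 − 78.11) = √89.67 = 9.47.
- Paired t test (noncentral t), two-sided 0.05, 95% power: n = 12, with power 0.963 at 12. Over r = 0 to 0.8, n runs from 20 down to 7.
- The text reads "would require a sample of 12 participants (alpha 0.5, 95% power"). Taken literally, alpha 0.5 needs 5 participants at r = 0.5 and at most 8 over that range of r. The stated 12 therefore fits two-sided 0.05, which is assumed from here on.

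**Number of tests in phase 1.**

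| Rating | Follow-up tests | Basis |
|---|---|---|
| MADRS | 3 | weekly to 2 weeks after the treatment week (the delayed arm has one more, not counted) |
| MoCA | 1 | before and after treatment |
| Q-LES-Q-SF | 1 | baseline and end of week 2 |
| QIDS | 3 | assumed weekly; no schedule is given |
| CGI-I | 0 | no baseline value to pair |

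The total is 3 + 1 + 1 + 3 = 8.

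**Family-wise rate when nothing changes on any scale.** For m independent tests it is 1 − 0.95^m:

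- m = 3: 1 − 0.8574 = 0.143
- m = 8: 1 − 0.6634 = 0.337

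The tests are not independent, because visits share a baseline and scales are related. Simulated paired t tests with n = 24 (60 × 0.4, the completers left by the planned 60% drop-out) and correlation 0.5 over time give:

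- MADRS, 3 tests: 0.128. A second simulation, with change scores correlated 0.5, gives 0.12 to 0.13; over change-score correlations of 0.3 to 0.8 the range is 0.10 to 0.14.
- All 8 tests: 0.314, 0.308 and 0.265 for between-scale correlations of 0, 0.3 and 0.6, that is, roughly 0.27 to 0.31.

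**One pre-named contrast.** The rate is 0.05 by construction. With 24 completers, power for the MADRS change at two-sided 0.05 is 0.983 at r = 0 and above 0.99 at r = 0.5.

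**The case against.** The strongest reply is that this is silence rather than error. The article condenses a fuller plan, and multiplicity rules are commonly left to the SAP. That stands as far as it goes: the absence of an adjustment is not the point here. What the article does state is a test per rating per visit, together with several different primaries, and that needs correcting whatever an SAP adds.

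Four stronger readings are tempting, and the document does not support them.

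- **That the trial has no ordering at all.** It has one powered contrast, named secondary outcomes, and an exploratory or pilot label on the second and exploratory aims. Those labels attach to the early-versus-delayed and left-versus-right questions, though, not to the other weeks and scales of the whole-sample change.
- **That running t tests before the ANOVA inflates error.** Order alone changes no error rate. The order only means that the ANOVA, as described, does not act as a gate.
- **That every test is declared at the full 0.05 level.** No level is stated for the analyses, so 0.05 is an assumption.
- **That the primary test itself has a false-positive rate several times 0.05.** The figures are rates for the whole family under a global null. Larger multiples need still more assumptions about QIDS and phase 2 visits, and remitters leave before phase 2.

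It is also fair to say that a global null is implausible for MADRS. Patients enter at 20 or above and the plan expects a fall from 25.4 to 14.1. Change unrelated to treatment is the larger threat in an uncontrolled comparison. The article admits that there is no sham control, and nothing proposed here cures that.

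**Conclusion.** The point holds in a limited form. The stated method produces several tests of change from baseline and does not tie the confirmatory claim to one of them, while the article's own primary definitions disagree. Under two-sided 0.05 per test and a global null, the chance of at least one false positive is about 0.12 to 0.13 for the three phase 1 MADRS visits. It is roughly 0.27 to 0.31 for the eight phase 1 tests, compared with 0.05 for one named contrast. The three-visit figure depends little on the correlation. The eight-test figure depends on the assumed weekly QIDS and should be read as an order of magnitude. The CGI-I point is small and needs no calculation, only that the scale rates improvement.

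**What to change.** In Statistical analysis, replace the sequence of paired tests with the following:

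1. Fit one repeated-measures model to the weekly MADRS scores.
2. Name the baseline-to-end-of-week-3 contrast from that model, the one the trial is powered for, as the only confirmatory test. Bring the Abstract and both clinical response sections into line with it.
3. Report the other MADRS weeks, QIDS and Q-LES-Q-SF as estimates with 95% confidence intervals, labelled exploratory.
4. Report MoCA change as a safety estimate with a 95% confidence interval whatever the efficacy result. Making it wait for a positive efficacy test could hide a cognitive harm signal.
5. Summarise CGI-I at each visit by its distribution or the proportion improved.

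A formal adjustment across the secondary ratings, such as Holm, is a matter of preference and is not needed if they are labelled exploratory.

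The cost is one rewritten paragraph plus the reconciled primary wording, with no new data and no larger sample. The small downside is that secondary results can no longer be presented as confirmatory on an unadjusted p-value.

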### Safety issues

Participants will undergo periodic observer-rated mood assessments during the study to check for any side effects or mood deterioration, including the emergence or exacerbation of psychiatric symptoms. In addition, before and after each TMS session, participants will be asked about any side effects or adverse events experienced. Responses will be documented, and spontaneous reports of the side effects will also be noted. An adverse event will be defined as any unfavorable medical change occurring that is accompanied by functional or clinical impairment. Participants who deteriorate to an unacceptable level during the trial (e.g., become acutely suicidal) will be withdrawn from the trial and appropriate clinical measures for their further treatment will be taken, including notification of their own treating doctor, referral to crisis team/community health center/public or private hospital.
Some participants have reported mild headache after TMS—this has not been problematic and has required mild analgesia at the most.The TMS device emits a clicking noise when it delivers the stimulation. There have been reports of hearing impairment in animals (permanent) and human participants (temporary) when TMS was given without the use of earplugs. Participants and experimenters will be provided with earplugs and/or protective headphones during TMS in this study.Seizures: Only a very small number of accidental seizures have been reported worldwide with TMS (*n*=11). Most of these have occurred with stimulus parameters outside current recommended safety guidelines [47]. There is no clear evidence of seizure induction with TMS in individuals who did not have an existing disorder which predisposes them to seizures. All TMS parameters used in this study are within safety guidelines. Our group has administered multiple sessions of TMS to over 26 subjects since November 2015 without accidental seizures or serious adverse effects. Safety precautions include training TMS staff in recognition and initial management of seizures. All subjects will be monitored for at least 30 min after each TMS session by trained staff nurses to monitor for possible seizures, headaches, or nausea*.*Pregnancy: there are at least 2 case reports of the safe use of repeated sessions of TMS (given in the first, second, and/or third trimester) to treat depression in pregnant women [48, 49]. Further, there are no theoretical reasons to suggest that TMS would pose a specific risk to the pregnant woman or fetus [49]. However, as the aim of the study is not to assess the safety of TMS in pregnancy, and as the risks of TMS in pregnancy are still relatively unknown, pregnant women will be excluded from the study.Mood switching: there are 6 case reports of TMS causing a mood switch into mania in participants with bipolar disorder [50]. The risk is relatively low, given the number of participants who have received TMS. Participants with unipolar depression who have had previous mood switching induced by an antidepressant treatment or with bipolar disorder will be advised that they may be at increased risk of mood switching with TMS and will be asked to consult their own doctor about the need for mood-stabilizing medication. There is no evidence that TMS is more likely to induce a manic switch than another course of antidepressant medication, i.e., the main alternative treatment for participants recruited into this study. Participants will be carefully monitored for mood changes suggestive of mood switching and if this occurs, will discontinue the trial and receive appropriate clinical treatment.

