Furthermore, the original FDA-approved protocol for rTMS, which to date has the largest evidence base, is the 10Hz L DLPFC protocol. This involves one session in each working day and patients need to come for the treatment for continuously 4 weeks. For those patients with no or poor response, additional 2 weeks of treatment by rTMS will be supplemented. Therefore, a standard course of unilateral TMS is about 38 min a day for 20–30 working days, substantially limiting the capacity of TMS services to meet the treatment needs of all patients. rTMS requires a considerable time commitment from both patients and clinicians and is of limited utility for patients who do not live within convenient traveling distance from treatment centers. The time needed before treatment response in some patients also makes rTMS unsuitable for some acutely suicidal patients. Accelerating the administration of rTMS (aTMS) by administering multiple sessions of rTMS over a shorter period of time has been shown to potentially be as efficacious as standard rTMS therapy [36–43]. These studies showed that aTMS was safe and efficacious, with no significant side effects reported, with a high level of patient acceptability and significant improvements in subjects’ depression after the aTMS. Thus, aTMS can potentially offer a more cost-effective treatment for depression than standard TMS that can help alleviate the large economic burden of depression by allowing patients to return to their work more rapidly.

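### The adverse event definition requires an undefined impairment, so expected mild effects such as headache fall outside any adverse event count

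*Protocol article*

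**What the plan says.** The definition stands in the protocol article under Safety issues: "An adverse event will be defined as any unfavorable medical change occurring that is accompanied by functional or clinical impairment". Neither that section nor any other says what counts as impairment, or who decides.

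The same section sets up wider data collection: "before and after each TMS session, participants will be asked about any side effects or adverse events experienced". It continues: "Responses will be documented, and spontaneous reports of the side effects will also be noted". This questioning carries no impairment threshold. The text thus uses two terms, side effects and adverse events, and defines only the second.

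The section then lists what may be expected. Headache comes first: "Some participants have reported mild headache after TMS", with the comment that "this has not been problematic and has required mild analgesia at the most". Hearing impairment, seizures and a switch into mania follow. Nurses are to watch each participant for at least 30 minutes after every session, and nausea is among the things they look for.

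**The concern.** An adverse event definition decides which observations enter the safety summary. If severity is part of the definition, events below the threshold disappear from the summary instead of appearing in it as mild. Here the threshold is also undefined, so two assessors could classify the same headache differently.

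The excluded events are of a kind that an accelerated schedule could make more frequent. Treatment at phase 1 gives 4 sessions a day on 5 weekdays, which is 20 sessions. A participant who enters phase 2 has another week, making up to 40. The Background supports acceleration partly with earlier work: "These studies showed that aTMS was safe and efficacious, with no significant side effects reported". The Discussion and Conclusions intend the results to inform treatment guidelines. A reader of those results would want to know how often a participant had any unwanted effect, and a count under this definition would not answer that.

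**Working it through.** The article states no adverse event rate, safety endpoint or safety sample size, so there is no figure to reproduce. The check has two steps.

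**Step 1. Set each expected effect against the definition.** All entries come from Safety issues.

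| Effect | What the article says | Meets the impairment condition? |
|---|---|---|
| Headache | mild, unproblematic, mild analgesia at most; no rate | As described, ordinarily no |
| Nausea | watched for after each session; no rate | If mild, probably no |
| Hearing impairment | temporary in people; no rate | Yes, it is named as an impairment |
| Seizure | 11 reported worldwide | Yes, on any ordinary reading |
| Switch into mania | 6 case reports; leads to leaving the trial | Yes |

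By type, 2 of 5 effects can fall outside the definition and 3 of 5 fall inside. Adding clinically relevant psychiatric deterioration, which the section also monitors and which would meet the condition, gives 2 of 6 outside.

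**Step 2. Direction and size of the effect on a reported proportion.** Let *p* be the proportion of participants with any unfavourable medical change. Let *s* be the share of those participants whose changes are all non-impairing. The proportion with an adverse event under the protocol's definition is

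(1 − *s*) × *p*.

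The relative shortfall is [*p* − (1 − *s*)*p*] / *p* = *s*. It is above zero whenever at least one affected participant has only non-impairing changes, and it can never be negative. The article gives neither *p* nor *s*. Over an assumed range for *s*:

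- *s* = 25%: (1 − 0.25)*p* = 0.75*p*, which is 25% lower
- *s* = 50%: (1 − 0.50)*p* = 0.50*p*, which is 50% lower
- *s* = 75%: (1 − 0.75)*p* = 0.25*p*, which is 75% lower

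The values of *s* are assumptions. Only the direction follows from the document.

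**The case against.** The strongest reply is that nothing is lost. Participants are asked at every session about any side effect, the answers are documented, spontaneous reports are noted, and nurses observe after each session. On this view the protocol has two reporting categories, the narrower one is labelled adverse event, and the full protocol or analysis plan, neither shown, may tabulate both. The article also names no adverse event rate as an outcome or analysis.

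Much of this stands. The mild events are captured, so the problem lies in classification and not in collection. A low figure arises only where a result is reported under the adverse event label. How the two categories are tabulated may properly be left to another document. But the definition itself is stated here without qualification, and collecting side effects under another name does not correct it.

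A second reply is that a headache needing analgesia after many sessions might be judged impairing. That is possible, because the term is undefined. It shows that the classification is unstable, which is a further reason to change the rule.

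Several stronger readings are tempting and are not supported:

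- A reader might infer that most expected TMS effects are excluded. By type this is wrong (2 of 5). By number of occurrences it is plausible, since serious effects are described as rare ("Only a very small number of accidental seizures have been reported worldwide with TMS"), but the article gives no frequencies for headache or nausea.
- Temporary hearing impairment might be cited as an excluded effect. The article calls it an impairment, so it meets the condition.
- A reader might infer that unblinded treating staff judge impairment. The article describes the study as open-label and single-blinded but does not say who classifies events.
- Tolerability might be taken as a main question of the trial. All three stated aims concern symptomatic efficacy or response.

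**Conclusion.** The point holds as a weakness in a stated rule. Impairment is required for an adverse event, is not defined, and leaves out mild headache and probably mild nausea, the first of which the protocol expects and both of which it monitors. Any adverse event proportion reported under this definition would understate the proportion of participants with any unfavourable change.

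The direction is certain as soon as one affected participant has only non-impairing events. The size is unknown: a 25% to 75% relative reduction corresponds to an assumed 25% to 75% of affected participants having only such events, and the article supplies nothing to narrow that range. A single before-and-after rate would suggest a precision that the document does not offer.

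This is a modest safety-reporting matter that is cheap to correct. It does not touch the efficacy analysis or the sample size.

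**What to change.** In Safety issues, replace the definition with one that counts any unfavourable medical change after the start of aTMS, whether or not it causes impairment and whether or not it is thought related to treatment. Record impairment as a severity grade (mild, moderate or severe), with a short description of each grade. State that the per-session side-effect responses and the spontaneous reports already documented are included. Report two numbers: participants with any event, and participants with an impairing event. The second preserves the information that the present definition was meant to give.

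The cost is a few lines of text, one extra column on the side-effect form and an adverse event figure that looks less favourable. No new visits, questions or participants are needed, because the responses are already collected.
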